### Active control group: non-adaptive computerized cognitive training

Participants assigned to the active control group will receive non-adaptive computerized cognitive training matched to the AI-Robot group in session frequency, approximate duration, visit setting, facilitator presence, and target cognitive domains. Control tasks will cover memory, attention, executive function, language, and orientation, with the same total planned dose of up to 72 sessions. The active control will be delivered on a tablet or computer using a standardized task library and scripted instructions. Facilitators may provide technical assistance, repeat standardized instructions, and monitor safety, but they will not provide individualized cognitive coaching or motivational dialogue beyond the control manual.

Instructions and feedback in the active control condition will be standardized and limited to neutral task guidance and correctness feedback. Task difficulty will follow a predefined progression schedule based on session number and task block rather than real-time performance or emotional state. The control condition will not include user-state vector generation, JITAI-based adaptation, LLM-generated dialogue, embodied robot social behaviors, or personalized emotional support. This design is intended to compare the complete adaptive embodied intervention package with a matched non-adaptive computerized control condition while aligning session dose, cognitive domains, visit environment, and facilitator contact as closely as feasible. Accordingly, the trial evaluates the package-level effect of adaptive embodied delivery supported by bounded LLM communication, rather than the isolated effect of the LLM component or the robot interface alone.

### AI system governance, fidelity, and risk management

To align with SPIRIT-AI reporting expectations, the LLM component, prompt templates, task library, adaptive decision rules, safety filters, and system version will be locked before the first participant is randomized (14). The trial master file will record the exact model identifier, provider, release date, parameter scale when disclosed by the provider, context-window limit, deployment mode, API endpoint or local hosting configuration, latency benchmark, prompt-template version, and any external tools or retrieval resources available to the model. The model, prompt set, task library, and thresholds will be frozen during the trial unless a protocol amendment is approved. Any system change will be logged with date, rationale, version number, validation result, and potential impact on intervention fidelity.

Prompt engineering will use a template-based strategy rather than free-form prompting. Each prompt will contain only the current task context, the structured user-state vector, the permitted response categories, safety prohibitions, and a short style guide for supportive language. The rule-based controller will pass only the selected action category and permitted communication style to the LLM. The LLM output will be checked against predefined wording categories, such as simplified instruction, encouragement, rest-break wording, or facilitator-review prompts. If model output is missing, unsafe, outside the permitted wording categories, or delayed beyond the prespecified latency limit, the system will fall back to scripted non-LLM prompts and the event will be logged.

The LLM will operate within a constrained intervention architecture. Inputs will be structured summaries of task performance and behavioral cues rather than unrestricted clinical records. Outputs will be limited to supportive conversational content and formatted messages for controller-selected actions consistent with the protocol. A rule-based safety layer will block or redirect outputs outside the intervention scope, including medical advice, stigmatizing language, excessive reassurance, unsupported memory claims, diagnostic labeling, or content that could increase distress. No online learning, model-weight updating, or autonomous change to the task library will occur during the trial.

A trained human facilitator will be present during each session. Facilitators will be trained to pause or terminate the session if the participant shows distress, fatigue, confusion that cannot be resolved by simplification, or any safety concern. Fidelity will be monitored through a structured checklist covering session dose, task order, permitted assistance, adherence to adaptation thresholds, safety-layer activation, adverse events, and deviations. At least 10% of sessions per facilitator per month and all flagged interactions will be reviewed by the research team. The target fidelity threshold is at least 85% adherence to checklist items; a facilitator or system component falling below 80% in any monthly audit, or any repeated safety-relevant deviation, will trigger retraining, technical review, and corrective documentation.

Participant privacy will be protected through de-identification, access control, encrypted storage, and data minimization. If cloud-based LLM processing is used, identifiable personal information will not be transmitted unless explicitly approved by the ethics committee and covered by institutional data-processing agreements. Audio, transcript, behavioral, and system-log data will be pseudonymized before analysis, stored on access-controlled institutional servers, and handled according to the approved data management plan.

### Adherence, retention, and concomitant care

Attendance, session completion, task exposure, rest breaks, session interruptions, and reasons for missed sessions will be recorded. Participants who miss a session will be contacted to reschedule within the same week when feasible. Strategies to promote retention will include flexible scheduling, reminder calls or messages, transportation guidance where available, and regular check-ins about fatigue and burden.

Participants will continue to receive usual care during the trial. Initiation of other structured cognitive training programs or participation in another cognitive intervention trial during the study period will not be permitted. Changes in medications, medical diagnoses, or relevant clinical events will be recorded and considered in sensitivity analyses when appropriate.

### Outcome measures

The schedule of enrollment, interventions, and assessments is summarized in Table 1. The adaptive intervention components, decision rules, permitted actions, and safety and fidelity controls are summarized in Table 2. Outcome measures will be administered by assessors blinded to group allocation. Validated Chinese versions of instruments will be used where available.

**Table 1 T1:** Schedule of enrollment, interventions, assessments, and post-intervention follow-up.

Study item	Screening/enrollment	Baseline	Weeks 1-24 intervention	Week 24 post-intervention	Week 36 follow-up
Eligibility screening	X				
Informed consent	X				
Demographics and medical history		X			
Randomization		X			
AI-Robot adaptive training			X		
Non-adaptive active control training			X		
MoCA primary outcome		X		X	X
Domain-specific cognitive battery		X		X	X
Emotional symptoms, motivation, usability, acceptance, expectancy, novelty, and social-presence measures		X	selected session-level logs	X	X
Adherence and engagement logs			continuous	summary	
Adverse-event monitoring			continuous	X	X
rs-fMRI and plasma biomarkers in nested sub-cohort		X		X	

**Table 2 T2:** Adaptive intervention components, decision rules, safety controls, and evidence/rationale.

Component	Decision rule or variable	Permitted action	Safety and fidelity control	Evidence/rationale
Cognitive task difficulty	Accuracy, latency, error pattern, and help requests; progress only after ≥80% accuracy and latency ≤ target for two consecutive blocks; de-escalate if accuracy <60%, latency >150% of target, or ≥2 help requests	Increase, maintain, decrease, or simplify task demand	Rule-based thresholds; de-escalation overrides progression; task library version-controlled	Maintains challenge while reducing overload and repeated failure
Instruction and feedback	Hesitation, confusion, incorrect responses, repeated instruction requests, and need for cueing	Repeat, rephrase, simplify wording, increase cueing, slow pacing, or adjust feedback frequency	Templates reviewed before trial; no diagnostic, prognostic, medication, or unsupported memory claims	Supports comprehension and comparable task exposure
Affective-motivational support	Facilitator-rated fatigue, distress, frustration, disengagement, and negative affective cues on a 0-3 checklist	Encourage, normalize errors, reduce demand, offer rest, or pause the session when rating ≥2	Rating 3, request to stop, or facilitator concern triggers stop rules	Protects comfort and reduces distress-related dropout
LLM communication module	Controller-selected action category, structured state vector, task context, and protocol constraints	Generate supportive wording only within the controller-selected action category	Frozen model/prompt version; parser restricts wording; unsafe or delayed output falls back to scripted prompts	Personalizes communication without autonomous adaptation
Session pacing	Fatigue, distress, attentional decline, prolonged latency, and participant request	Slow pace, shorten block, initiate rest, reschedule activities, or terminate session	Stop rules, adverse-event reporting, facilitator training, and monthly audit	Balances intervention dose with safety and tolerability
Human oversight and fidelity audit	Session logs, transcript samples, safety flags, deviations, and facilitator checklist scores	Review ≥10% of sessions per facilitator per month plus all flagged interactions	Target fidelity ≥85%; <80% monthly adherence or repeated safety deviation triggers correction	Supports reproducibility, accountability, and SPIRIT-AI transparency

The primary outcome is change in global cognitive function from baseline to week 24, measured by MoCA score. Maintenance of MoCA change from week 24 to week 36 and between-group difference in MoCA change from baseline to week 36 will be analyzed as secondary exploratory durability outcomes.

Secondary cognitive outcomes will assess domain-specific performance. The planned battery includes the Auditory Verbal Learning Test for episodic memory, Trail Making Test Part A for attention and processing speed, Trail Making Test Part B and the Clock Drawing Test for executive and visuospatial function, Digit Span Forward and Backward for attention and working memory, semantic verbal fluency for language and semantic retrieval, and orientation items captured within the MoCA or locally validated measures.

Secondary emotional and motivational outcomes will include depressive symptoms measured by the Geriatric Depression Scale-15, anxiety symptoms measured by the Generalized Anxiety Disorder-7 scale, apathy measured by the Apathy Evaluation Scale, training motivation measured using the Intrinsic Motivation Inventory interest/enjoyment and effort/importance subscales or a locally validated equivalent, perceived engagement measured using the User Engagement Scale-Short Form plus session-level logs, technology acceptance using an older-adult digital health or robot acceptance questionnaire, usability measured by the System Usability Scale, and brief expectancy, novelty, and perceived social-presence items to help interpret potential expectancy and novelty effects. Behavioral engagement will also be captured through session attendance, completed tasks, time on task, response latency, help requests, rest breaks, and dropout.

Safety outcomes will include adverse events, serious adverse events, intervention-related distress, fatigue, falls or near falls during visits, clinically significant anxiety or frustration during sessions, and technical failures that affect participant safety or data integrity. All adverse events will be recorded, graded, and reviewed according to the approved study procedures.

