### Randomization and blinding

After eligibility confirmation and baseline assessment, eligible participants will be randomized to the AI-Robot group or active control group using a computer-generated block randomization sequence with a 1:1 allocation ratio. The allocation sequence will be generated by an independent researcher who is not involved in recruitment, intervention delivery, outcome assessment, or data analysis. Allocation concealment will be maintained using sequentially numbered, opaque, sealed envelopes until the participant has completed baseline assessment and has been formally enrolled.

Because of the nature of the intervention, participants and intervention facilitators cannot be blinded to group assignment. Outcome assessors, MRI analysts, laboratory staff, and statistical analysts will remain blinded to group allocation until the primary analysis has been completed. Participants will be reminded not to disclose group assignment to outcome assessors.

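### Blinded assessors are also assigned the acceptance, usability and social-presence measures, which are likely to disclose the arm at the visits where the MoCA is scored

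*Protocol article*

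**What the plan says.** Under Outcome measures the article gives one rule on who collects outcomes: "Outcome measures will be administered by assessors blinded to group allocation". No instrument is set apart.

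The secondary outcomes in the same section include "technology acceptance using an older-adult digital health or robot acceptance questionnaire". The System Usability Scale is named for usability, and a few short items are planned on expectancy, novelty and how socially present the system felt.

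Table 1 has one row for "Emotional symptoms, motivation, usability, acceptance, expectancy, novelty, and social-presence measures". It is marked at baseline, week 24 and week 36, the same three time points as the row "MoCA primary outcome". The table gives no order of tests within a visit.

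Under Randomization and blinding, participants and facilitators are acknowledged to be unblinded. Outcome assessors, among others, "will remain blinded to group allocation until the primary analysis has been completed". The only safeguard given for the assessors is a reminder to participants not to reveal their group. The section on the active control states that this arm has no robot social behaviors and no LLM dialogue.

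**The concern.** Two commitments pull against each other. One keeps the assessor ignorant of the arm. The other, as written, has that assessor question an unblinded participant about the device or program that defines the arm. A reminder can discourage a chance remark, but it does not protect against an answer that the assessor's own question invites.

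The MoCA is administered and scored by an examiner. Because participants and facilitators are unblinded, assessor blinding is what protects its scoring. Once an assessor knows a participant's arm, that knowledge carries to every later test with the same participant, and the scores cannot be re-blinded afterwards.

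**Working it through.** **1. The texts side by side**

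| Question | What the article states | Where |
|---|---|---|
| Who collects outcomes? | Blinded assessors, no exception stated | Outcome measures |
| Are device-experience measures outcomes? | Yes: acceptance, usability, engagement, expectancy, novelty, social presence | Outcome measures |
| When? | Baseline, weeks 24 and 36, as for the MoCA | Table 1 |
| Do participants know their arm? | Yes | Randomization and blinding |
| Do both arms use a robot? | No, only the intervention arm | Interventions |
| What protects the assessor? | A reminder to participants | Randomization and blinding |

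**2. Where exposure can arise**

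- Baseline: none. Randomization follows the baseline assessment, so there is no arm to disclose.
- Week 24, device measures before the MoCA: the primary score is exposed.
- Week 24, MoCA first: the primary score is protected. Any test given after the device measures is exposed.
- Week 36, same assessor as at week 24: the MoCA and cognitive battery are exposed whatever the order on the day.

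**3. Would the answers disclose the arm?** An acceptance form that differs by arm identifies the arm by itself. A common form may not, but the answers can still be informative: the Discussion expects expectancy, novelty and perceived social presence to differ possibly between groups, and says they are measured for that reason. Disclosure is therefore a strong inference, not something the documents state.

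**4. Illustration of size**

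The plan's own figure first (Sample size: difference 1.6, SD 3.0, two-sided alpha 0.05, power 80%), by the normal approximation:

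n = 2 × (1.960 + 0.842)² × 3.0² / 1.6² = 55.2, so 56 per group; 56 / 0.90 = 62.2, so 63. Both match the article, and this point does not dispute them.

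Now let the true effect be 0 and let unblinded scoring shift the whole between-arm difference by b. The values of b are assumptions; the documents give none. With 63 × 0.90 = 56.7 analyzed per arm:

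SE = 3.0 × √(2 / 56.7) = 0.563

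P(reject) = 1 − Φ(1.96 − b/SE) + Φ(−1.96 − b/SE)

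| Assumed b (points) | b / SE | Type I error |
|---|---|---|
| 0 | 0 | 5% |
| 0.25 | 0.44 | about 7% |
| 0.5 | 0.89 | about 14% |
| 1.0 | 1.78 | about 43% |

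With 56 per arm the last three are 7%, 14% and 42%. A shift of 0.5 is 0.5 / 1.6 = 31% of the planned difference.

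**5. End of blinding.** The blinding commitment ends with the primary analysis, whose endpoint is at week 24. Recruitment from September 1, 2026 to September 30, 2027 spans 395 days, and week 36 falls 84 days after week 24. With uniform accrual, the week-36 visits outstanding when the last participant reaches week 24 are 126 × 84 / 395 = 26.8, about 27. This ignores attrition and assumes the primary analysis is finished that same day, so it is an upper bound.

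**The case against.** The strongest reply is that the rule is a generic summary sentence. It cannot cover everything listed as an outcome, since attendance, session logs and technical failures are not administered by anyone. Order of tests, staffing and mode of completion usually sit in a manual that is not shown. The acceptance instrument may be the digital-health option, the System Usability Scale is named without arm-specific wording, and the novelty and social-presence items are not reproduced. Table 1 also marks this row at baseline, before any arm exists, which suggests either neutral wording or a grouped row that should not be read item by item.

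Much of this stands. A reader might infer that a robot questionnaire is fixed, that the arm is certain to be revealed, or that following the plan defeats the blinding of the primary outcome. The documents support none of these: the instrument is left open, disclosure is inferred, and no order is stated, so a MoCA given first at week 24 is untouched. The week-36 MoCA is a secondary exploratory outcome. No text says that the primary analysis will precede the last week-36 visit, and only one database lock is mentioned.

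What does not stand is that this is merely omitted detail. The article does say who administers the outcomes, and the questionnaires are administered instruments that fall within that rule. As worded, the rule works against the blinding promised elsewhere in the same article.

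**Conclusion.** The concern holds in a limited form. The rule on administration has blinded assessors give measures likely to disclose the arm at the same time points as the MoCA, and the stated safeguard cannot prevent it. The primary week-24 score is at risk only if those measures come before the MoCA. Otherwise the risk lies with the week-36 MoCA and cognitive battery when the same assessor returns.

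The type I error figures are illustrations that assume a uniform, directional shift across the whole contrast; they do not measure this trial's bias. The figure of about 27 visits applies only if the primary analysis is completed as soon as the last participant reaches week 24. The sample size is unaffected. Recruitment had not started at resubmission, so the repair can be made before any score is exposed.

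**What to change.** - In Outcome measures, restrict the blinded-assessor sentence to the MoCA, the cognitive battery and the symptom scales, and state that at each visit these are completed before any device-experience measure.
- Have the acceptance, usability, engagement, novelty, expectancy and social-presence measures self-completed afterwards, or given by existing non-blinded staff, preferably not the participant's own training facilitator. Withhold the responses from the assessor.
- In Randomization and blinding, extend assessor blinding through the last week-36 assessment.

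The cost is wording and visit order, with no extra staff and no change in sample size. The downside is small: some participants will need help with reading, and help from staff who deliver the training may invite courtesy answers on these secondary scales.

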### Neuroimaging and biomarker sub-cohort

A nested exploratory imaging-biomarker sub-cohort of approximately 50 participants (target 25 per group), subject to MRI eligibility, consent, and feasibility, will undergo rs-fMRI and plasma biomarker testing at baseline and week 24. MRI eligibility will be assessed separately, and contraindications to MRI will exclude only participation in the imaging component. Because this sub-cohort is not powered for confirmatory mechanistic inference, all imaging and biomarker analyses will be treated as exploratory and hypothesis-generating.

The rs-fMRI acquisition and preprocessing framework will be locked in an imaging manual before the first imaging visit. The minimum MRI protocol will include high-resolution three-dimensional T1-weighted structural imaging and resting-state echo-planar functional imaging on a 3.0-T scanner, with scanner model, sequence parameters, head-motion monitoring, eyes-open or eyes-closed instruction, and acquisition duration recorded for reproducibility. Preprocessing will include discarding initial volumes, slice-timing correction when applicable, realignment, co-registration, normalization to standard space, spatial smoothing, nuisance regression, temporal filtering, and motion scrubbing. Participants with excessive motion, defined *a priori* using framewise-displacement and gross-motion thresholds, will be excluded from affected imaging analyses. ROI analyses will focus on standard atlas-defined DMN and CEN regions, including posterior cingulate/precuneus, medial prefrontal cortex, lateral parietal cortex, dorsolateral prefrontal cortex, and posterior parietal executive-control regions. Whole-brain exploratory analyses may be conducted using appropriate correction for multiple comparisons.

Blood samples will be collected to measure biomarkers related to neuroplasticity and neurodegeneration. Planned markers include brain-derived neurotrophic factor (BDNF), phosphorylated tau 181 (p-tau181), and neurofilament light chain (NfL), which may provide complementary information about synaptic plasticity and Alzheimer disease-related pathology or neuroaxonal injury (33). Venous blood will be collected into prespecified tubes, processed within the laboratory manual time window, aliquoted to avoid repeated freeze-thaw cycles, and stored at −80°C until analysis. BDNF will be measured using a validated immunoassay kit, and p-tau181 and NfL will be measured using validated ultrasensitive immunoassay platforms when available. Batch structure, duplicate testing, calibration, lower limits of quantification, coefficient-of-variation thresholds, and procedures for out-of-range values will be specified before sample analysis.

### Sample size

The planned sample size is 126 randomized participants, with 63 participants in each group. The calculation is based on the primary endpoint, defined as change in MoCA score from baseline to week 24. The assumed between-group difference of 1.6 MoCA points and common standard deviation of 3.0 points were selected as a plausible intervention effect for trial planning, informed by prior computerized or multi-domain cognitive training trials and reviews in older adults with cognitive impairment (5, 23, 24). This assumption is used for sample-size estimation only and is not presented as a universal minimal clinically important difference. The study is designed to test whether the intervention can detect a plausible efficacy signal within a feasible single-center protocol, rather than to establish a definitive clinically important difference threshold. With a two-sided alpha level of 0.05 and 80% statistical power, 56 participants per group are required. Allowing for approximately 10% attrition, the target sample size is inflated to 63 participants per group, yielding a total sample size of 126 participants.

Sensitivity calculations using the same alpha, power, and standard deviation assumptions indicate that detectable between-group MoCA differences of 1.0, 1.2, 1.4, 1.6, 1.8, and 2.0 points would require approximately 142, 99, 73, 56, 44, and 36 participants per group before attrition, respectively; after allowing for 10% attrition, the corresponding targets are approximately 158, 110, 82, 63, 49, and 40 participants per group. The nested imaging-biomarker sub-cohort target of approximately 25 participants per group is feasibility-based and will be used for exploratory estimates of effect direction, variance, and brain-behavior associations rather than confirmatory hypothesis testing.

